#### Unexpected Adverse Drug Reaction (UADR)

An “unexpected” adverse drug reaction is an adverse reaction, the nature or intensity of which is not consistent with the list of AEs provided above in this chapter.

#### Suspected Unexpected Serious Adverse Reactions (SUSARs)

InnoMedica evaluates any SAE that will be reported regarding seriousness, causality and expectedness. If the event is related to the investigational product and is both serious and unexpected and not listed as possible AE, it will be classified as a SUSAR.

#### Assessment of Intensity

| Grade | Type             | Description                                                                                                                                                                    |
|-------|------------------|--------------------------------------------------------------------------------------------------------------------------------------------------------------------------------|
| 1     | mild             | Awareness of a sign or symptom that does not interfere with the trial participant's usual activity or is transient, resolved without treatment and with no sequelae            |
| 2     | moderate         | Interferes with the trial participant's usual activity and/or requires symptomatic treatment.                                                                                  |
| 3     | severe           | Medically significant, but not life-threatening. Symptom(s) causing severe discomfort and significant impact of the trial participant's usual activity and requires treatment. |
| 4     | Life-threatening | Emergency intervention needed.                                                                                                                                                 |
| 5     | lethal           | Death due to SAE.                                                                                                                                                              |

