#### 3.4.4 Clinical safety of TLN's excipients

Eventual excessive cholesterol or sphingomyelin enrichment are expected to be identified through collected lab values and should be reversible once the dose is lowered or treatment is suspended. In the routine lab analyses, liver enzymes will be monitored. Provided no enzymatic deficiencies like lipid storage disorders (e.g., gangliosidosis) are present, which would lead to a study exclusion in the first place, all molecules of TLN will enter the natural turnover of the respective molecular species. A 30 mL vial of TLN contains 180 mg of liposomal GM1; [REDACTED]

[REDACTED]. The USFDA recommends a maximum dose of 300 mg of cholesterol daily, while no recommendation exists for sphingomyelin, daily dietary uptake of sphingolipids is evaluated at 400 mg. Use of TLN could then be compared to dietary uptake of these lipids. At the maximum planned dose of TLN, [REDACTED] will be injected, compared to weekly dietary uptake and/or recommended dose (2800 and 2100 mg respectively) both excipients remain in the range of a weekly dietary consumption and should not overly imbalance these two metabolites.

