### 5.1 Primary Outcomes

The primary outcome of this trial is safety, designed as the measurement of:

- Occurrence of AEs
- Occurrence of SAEs
- Occurrence of any routine lab test values out of normal range including anti-GM1 antibodies and apolipoprotein B.

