### **6.2.3 Other methods of minimising bias**

For the primary endpoint, the assessments of the outcome are based on standards and norms. In this trial, the following validated instruments will be used to assess secondary endpoints: MDS-UPDRS, PDQ-39, ESS, NMSQuest, SAS, BDI, and MoCA.

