#### Part 1 – Dose escalation:

| Causality            | Intensity   | Resolution until next infusion | Next patient added/ Dose increase                                                                                                         |
|----------------------|-------------|--------------------------------|-------------------------------------------------------------------------------------------------------------------------------------------|
| (unlikely/unrelated) | grade 1 - 3 | yes/no                         | yes                                                                                                                                       |
| Possible             | grade 1     | yes                            | yes                                                                                                                                       |
| Possible             | grade 1     | no                             | yes                                                                                                                                       |
| Possible             | grade 2     | yes                            | yes                                                                                                                                       |
| Possible             | grade 2     | no                             | Delay till resolution (maximum of 3 weeks), then rechallenge at same dose level, if re-occurrence stop treatment for the affected patient |
| Possible             | grade 3     | yes/no                         | no (stop treatment for the affected patient but others to continue)                                                                       |
| Probable/definite    | grade 1     | yes/no                         | yes                                                                                                                                       |
| Probable/definite    | grade 2     | yes                            | yes                                                                                                                                       |
| Probable/definite    | grade 2     | no                             | no (stop treatment for the affected patient but others to continue)                                                                       |

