Safety lab values will be assessed from blood collection performed every week during part 1 (3 days after TLN infusion) and part 2 (on the day of TLN infusion) according to the schedule. Abnormal

values will be compared to the normal range provided by the laboratory (**Annex 2**), then assessed by the PI for grading. All analyses will be performed from venous blood collection before the infusion. Samples will be collected on each sampling day by courier by Viollier and processed in their facilities.

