### 10.1 Definition and assessment of (serious) adverse events and other safety related events

An **Adverse Event (AE)** is any untoward medical occurrence in a patient or a clinical investigation participant who was administered a pharmaceutical product and which does not necessarily have a causal relationship with the study procedure. An AE can therefore be any unfavourable and unintended sign (including an abnormal laboratory finding), symptom, or disease temporally associated with the use of a medicinal (investigational) product, whether or not related to the medicinal (investigational) product.

AEs (and SAEs) will be documented by the PI and collected and documented in the DB.

A **Serious Adverse Event (SAE)** is classified as any untoward medical occurrence that:

- results in death,
- is life-threatening,
- requires in-patient hospitalization or prolongation of existing hospitalisation,
- results in persistent or significant disability/incapacity, or
- is a congenital anomaly/birth defect.

In addition, important medical events that may not be immediately life-threatening or result in death, or require hospitalisation, but may jeopardise the patient or may require intervention to prevent one of the other outcomes listed above should also usually be considered serious.

SAEs should be followed until resolution or stabilisation. Participants with ongoing SAEs at study termination (including safety visit) will be further followed up until recovery or until stabilisation of the disease after termination.

In order to standardise all AEs, they will be coded according to the Medical Dictionary for Regulatory Activities (MedDRA). Adverse events and SAEs will be summarized by body system and preferred term based on the Medical Dictionary for Regulatory Activities (MedDRA).

A **Suspected Unexpected Serious Adverse Reaction (SUSAR)** will be assessed based on possible AEs.

As there are no data for TLN in humans available, the following list of possible AEs is based on literature from clinical trials in which GM1 was applied in different galenic forms and dosages. If any of these AEs would appear in the trial, they would be judged as "expected" AEs.

- Local pain
- Pruritus
- Vasovagal reaction
- Urinary tract infection
- Mild head soreness
- Nocturnal confusion
- Exfoliative dermatitis
- Mild meningitis
- Slightly increased CSF/serum albumin
- Increase in systolic blood pressure
- Hyperreflexia
- Transient rash
- Conjunctivitis

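### Laboratory AEs are graded on a scale built on symptoms and daily activity, so the same silent abnormality can be graded 1 (dose may rise) or 3 (treatment stops if related), with no criterion to separate the two

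*Protocol*

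**What the plan says.** Section 10.1 defines an adverse event as "any unfavourable and unintended sign (including an abnormal laboratory finding), symptom, or disease", so a laboratory abnormality is an AE. Section 9.2.1 compares each abnormal value with the laboratory's normal range in Annex 2; it is "then assessed by the PI for grading".

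The protocol contains one intensity scale, the table under Assessment of Intensity in section 10.1. Grade 1 is "Awareness of a sign or symptom that does not interfere" with usual activity, or one that is transient. Grade 2 requires interference with activity, symptomatic treatment, or both. Grade 3 opens with a sentence on medical significance, followed by a second sentence that requires symptoms with severe discomfort, an effect on activity and treatment. Grade 4 is life-threatening and turns on emergency intervention. No grade mentions a laboratory value.

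The grade, with causality and resolution, enters the matrices of section 8.3. In Part 1 the outcome column is headed "Next patient added/ Dose increase"; in Part 2 it is whether the dose is repeated. Section 11.4.2 tabulates AE intensity in the primary safety analysis.

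Laboratory values also appear directly in section 5.1, as "Occurrence of any routine lab test values out of normal range including anti-GM1 antibodies and apolipoprotein B".

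**The concern.** The scale asks what the patient feels and can do. A raised liver enzyme, lipid or antibody value often produces neither a symptom nor a limit on activity, so the scale does not distinguish a small deviation from a large one.

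This matters here because the protocol itself expects effects of this kind. Section 3.4.3 reports that repeated high-dose GM1 in healthy volunteers raised cholesterol, triglycerides and apolipoprotein B and had no other observed effect. Section 3.3.4 reports that adverse effects at the higher rat doses were mostly histopathological findings and changes in blood and chemistry values. Section 3.4.4 says that excess lipid from the excipients is "expected to be identified through collected lab values and should be reversible once the dose is lowered or treatment is suspended".

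Three things are at stake: whether a patient moves to the next dose level, the maximal suitable dose (MSD) averaged from three patients and given to nine more, and the consistency of the AE intensity table.

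**Working it through.** No sample size or power figure is involved. The check reads a silent laboratory value against each grade and then follows the grade through the matrix.

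**1. Reading the value against the scale.** Annex 2 gives ALT an upper limit of 40 U/L. Take two hypothetical values, 60 and 400 U/L: 60/40 = 1.5 and 400/40 = 10 times the limit. Assume no symptoms, no effect on activity and no treatment.

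- Grade 1: the condition of no interference with activity is met by both values.
- Grade 2: not met by either.
- Grade 3: the first sentence can be met if the investigator considers the value medically significant. The second sentence is not met by either.
- Grade 4: met only if the value is judged life-threatening and in need of emergency intervention.

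Both values fully meet only the grade 1 wording, and either can be placed in grade 3 through that grade's first sentence. The text gives no point between 1.5 and 10 times the limit, or anywhere else, at which the grade changes.

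**2. Following the grade through the Part 1 matrix.** Three causality classes × three grades × resolved or not = 18 cells. The cells that allow the dose increase are:

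| Grade | All causality classes | Possible or probable/definite only |
|---|---|---|
| 1 | 6 of 6 | 4 of 4 |
| 2 | 4 of 6 | 2 of 4 |
| 3 | 2 of 6 | 0 of 4 |

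Grade 1 allows the increase even when the event is probably or definitely related and has not resolved. A related grade 3 event stops treatment for at least the affected patient. The Part 2 matrix has the same 4, 2 and 0 of 4 pattern for repeating the dose.

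**3. Effect on the MSD.** Section 9.2.2 averages the highest doses reached by three patients. From dose level 3 upward the steps are 60 mg. One step in one patient moves the MSD by 60/3 = 20 mg; one step in all three moves it by 60 mg. As an illustration, suppose a related silent finding arises in one patient at 360 mg. If it is graded 3, that patient's maximum stays at 360 mg. If it is graded 1 and nothing else intervenes, the patient can reach 720 mg. The MSD then differs by (720 − 360)/3 = 120 mg.

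**4. Where the grade does not act.** Section 5.1 counts any out-of-range value. ALT of 60 and ALT of 400 both count once as out of range, whatever the grade.

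**The case against.** The strongest objection is that grade 1 is not forced. Grade 3 allows medical significance to be considered, grade 4 does not depend on symptoms, and grade 1 speaks of awareness, which a silent value does not clearly satisfy. This stands. A reader might infer that every silent abnormality must be graded 1, or that all analytes behave alike. The text does not support either: a large deviation in potassium or platelets, for example, could call for emergency intervention. What remains is that the choice has no stated criterion.

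A second objection is that the investigator does not decide alone. Under sections 1.6 and 10.1.1 the Internal Monitoring Committee (IMC) reviews AEs weekly. It must be unanimous on continuing each patient, and it includes an independent external physician. The DSMB reviews raw data, including after dose levels 5 and 10. An important medical event can be classed as serious, and with one narrow exception an SAE stops treatment. Medical judgement is also a ground for withdrawal. These are real safeguards, and it would be wrong to say that one rater decides. They remain discretionary, however, and the protocol gives them no laboratory criterion.

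Three further inferences are tempting but not supported:

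- **That the laboratory part of the primary outcome is biased.** It is a yes/no count and does not use the grade. The synopsis does not list it as primary at all.
- **That section 6.2.3 is contradicted.** It says "For the primary endpoint, the assessments of the outcome are based on standards and norms". Reference ranges, ICH E2A causality and MedDRA coding fit that sentence, which does not promise numeric toxicity grading.
- **That section 3.4.4 cannot be squared with the matrix because the matrix never lowers a dose.** Section 3.4.4 also names suspension, and the matrix contains delay and stop. The sentence predicts reversibility and sets no rule. The gap is only that a silent finding graded 1 triggers neither delay nor stop.

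Finally, section 10 refers to a safety management plan that is not shown. It may hold laboratory grading, but the protocol does not point to it for that purpose.

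**Conclusion.** The concern holds as a defect in the grading rule. A silent laboratory AE of any size can be graded 1 or 3. If the event is at least possibly related, the first reading allows escalation in 4 of 4 matrix cells and the second in 0 of 4. The consequence reaches the escalation decision, the MSD (20 mg for each 60 mg step in one patient) and the AE intensity table. It does not reach the out-of-range count in section 5.1.

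This rests on the protocol's wording, on a value without symptoms or treatment, and on there being no laboratory grading in the safety management plan. The ALT values and the 120 mg example are illustrations, not forecasts. The documents do not show that a dose would rise unsafely, since the IMC can withhold it. They show that nothing written would make two raters, or two meetings, treat the same value alike. Because the grade is used during dosing, an analysis plan written for the end of the trial cannot repair it. The protocol should be changed.

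**What to change.** Before dosing, name in section 10.1 one published laboratory grading scale for the intensity of laboratory AEs. The sponsor's clinicians should choose it, and it should suit both one-sided analytes such as ALT and two-sided ones such as sodium and potassium; plain multiples of the Annex 2 limits would not serve for all. Keep the present scale for clinical AEs. Use the same laboratory grade wherever AE intensity is used, including the section 11.4.2 tabulation.

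Reconcile sections 3.4.4, 8.3, 9.2.1 and 10.1 so that they agree on what a laboratory finding leads to. The content of that rule is for the sponsor's clinicians; no threshold or dosing consequence is proposed here. If the safety management plan already contains a laboratory scale, a cross-reference from sections 9.2.1 and 10.1 would be enough for the grading part.

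The cost is one table or reference in section 10.1 and grading programmed in the eCRF. The downside is that some silent findings will grade higher than they would now and may slow or stop escalation.

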### 3.7 Risks / Benefits

According to the literature and non-clinical data of TLN, the profile of TLN is expected to be very safe. All components of TLN are metabolites that can be produced and broken down by the human body. There is very little risk of accumulation based on current knowledge. The known risks associated with GM1 from the literature are detailed in section **3.4.3 Clinical safety**. For the patients following the escalation schedule, the main risk is that TLN will be given for the first time in human as i.v. infusion. This is mitigated by a very low starting dose and a careful follow-up and escalation. The main risk potentially associated with TLN is an over performance compared with free GM1. Talineuren could reach the brain cells more efficiently than the free drug GM1 and might cause cerebral symptoms with disorientation, confusion, and headache similarly to what was observed in the trial using 50 mg intracranial injections on GM1. With a liposomal formulation i.v. injected by continuous infusion that could be stopped if encephalopathic side effects appeared, sudden local increase of GM1 (e.g., in the brain) will be avoided and therefore this risk is considered minimal.

There are also risks inherent to the weekly i.v. injections and the local pain caused by this repeated procedure over 8 or 14 weeks.

The potential benefit is a disease-modifying treatment that may slow down or even halt the progression of the disease by reduction of the neuronal decay, which could preserve functioning neurons and prevent symptoms from appearing or worsening. GM1 has been shown to increase neuronal survival and reduce neuroinflammation. This has been observed and documented *in vitro* and *in vivo*. First beneficial effects (in terms of UPDRS score reduction, with 6 points improvement) may be noticeable as early as after 6 weeks of treatment. The patients might clinically benefit from the drug even though this is only a phase I trial.

One potential risk identified is the potentially reduced need for levodopa in case that there was a significant therapeutic effect of TLN over the course of this trial. If the patients' condition improves the prescribed dose of levodopa might become too high. The levodopa treatment (or other similar medication) will then be continuously re-assessed during the trial by the PI and adjusted as clinically needed for the best care of the patient.

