#### 6.1.1 Dose escalation (Part 1)

In this part a group of 3 patients will receive a single weekly dose that will be increased according to the schedule defined. In parallel, meaning that the first patient will receive a dose X on week Y, if the safety assessment is positive (see **Section 8.3 Dose modifications**) then the following week (Y+1) this patient will receive the next dose (X+1), on that week (Y+1) two other patients will receive the same dose X to confirm the safety assessment. *In fine*, every week patient 1 will receive one dose at the same time that patients 2 & 3 receive the preceding dose.

This weekly increase has been elected to allow rapid determination of the MSD and rapidly reach a dose level that will be beneficial for the patients involved in this trial. This is allowed by the fact that GM1 is expected to be safe and no clear AE are foreseen within this dose range. Furthermore, the 1 + 2 pattern allows one week observation of each dose increase in 1 patient before infusing 2 more.

The first dose level starts at 6 mg which will increase to 12 and 60 mg, then increasing by equal steps of 60 mg up to 720 mg. The escalation will be stopped individually according to the decision matrix detailed in the **Section 8.3 Doses modifications**. The three first steps of the dose are purposely low to account for any possible unexpected effects of the formulation.

Throughout the escalation part, all patients will be monitored twice weekly to record AEs and document them. Monitoring will take place once before each TLN infusion (beginning of the week) and a second time by the end of each week (performed by the principal investigator) to collect AE and allow enough time for the IMC to review them and take their decision on the next infusion/dose modification/delay.

At the end of the escalation, the average of the three maximum tolerated doses by the three patients will be defined as MSD for part 2. With this design, we aim to find the highest dose that generates, if any at all, at maximum only transient mild/moderate AEs. At the same time, this will allow to glean information on clinical effect for the planning of a potential phase II study.

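### The adverse event intensity grades overlap: a brief, untreated event that interfered with usual activity fits grade 1 and grade 2, and the grade 3 boundary is unclear for a severe event that needed no treatment

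*Protocol*

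**What the plan says.** The table under Assessment of Intensity in Protocol section 10.1 defines the grades.

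- **Grade 1** covers awareness of a symptom that does not interfere with "usual activity or is transient, resolved without treatment and with no sequelae". The two routes are joined by an or.
- **Grade 2**: "Interferes with the trial participant's usual activity and/or requires symptomatic treatment". Interference alone is enough, and short events are not excepted.
- **Grade 3** has two sentences. The first is "Medically significant, but not life-threatening", with no further definition. The second is "Symptom(s) causing severe discomfort and significant impact of the trial participant's usual activity and requires treatment".

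Intensity is used in two places. Section 11.4.2 lists it among the key data of the primary safety analysis. The Part 1 matrix in section 8.3 combines it with causality and with a separate column, "Resolution until next infusion", to decide whether the dose rises. Section 6.1.1 states the aim as the highest dose with "at maximum only transient mild/moderate AEs", so it treats duration and severity as two attributes. Sections 6.1.1 and 9.2.2 set the MSD as the average of the three Part 1 patients' maximum doses, and nine Part 2 patients receive it.

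Section 3.7 says that TLN "might cause cerebral symptoms with disorientation, confusion, and headache" if it reaches the brain more efficiently than free GM1. It adds that the infusion could be stopped if such effects appeared, and it calls the risk minimal.

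**The concern.** An intensity scale should give each event one grade. Here duration and resolution are built into grade 1 while functional impact defines grade 2, so one event can satisfy both. Consider a patient who is disoriented and unable to function for two hours during an infusion, then recovers without treatment and without sequelae. One reader could record grade 1, another grade 2, and a third could argue for grade 3 on medical significance.

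Two things are at stake. The first is the intensity tabulation in an open-label trial without a control group, where section 6.2.3 relies on standards and norms to limit bias in the primary endpoint. The second is the escalation decision, if the ambiguity reaches a boundary where the matrix answers differently. The check below separates the two.

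**Working it through.** No sample size or power figure is involved, and section 11.2 says that none was calculated. The check is one of logic.

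**Step 1. Which grades fit?** Take an event that is transient and leaves no sequelae, and apply the section 10.1 definitions.

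| Interferes | Treated | Grade 1 | Grade 2 | Grade 3, second sentence |
|---|---|---|---|---|
| no | no | yes | no | no |
| yes | no | yes (transient route) | yes | no |
| yes | yes | no | yes | yes, if discomfort and impact are severe |
| no | yes | depends on how the sentence is parsed | yes | no |

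The second row is the point at issue. The overlap holds whether the conditions on treatment and sequelae attach to the transient route alone or to both routes. If the event was also severe, the second sentence of grade 3 fails on treatment, but the first sentence might be satisfied. Grades 1, 2 and 3 are then all arguable.

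The table also does not say whether stopping the infusion counts as treatment. If it does, an event ended in that way loses the transient route to grade 1 and meets the treatment condition of grade 3. If it does not, the reverse holds.

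**Step 2. Where does the grade change the dose decision?** The Part 1 matrix in section 8.3 has ten rows for related events: three for grade 1, four for grade 2 and three for grade 3.

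| Causality | Resolved by next infusion | Grade 1 | Grade 2 | Grade 3 |
|---|---|---|---|---|
| possible | yes | increase | increase | stop patient |
| possible | no | increase | delay, then rechallenge | stop patient |
| probable/definite | yes | increase | increase | stop patient |
| probable/definite | no | increase | stop patient | stop all patients |

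An event can use the transient route only once it has resolved. In both resolved rows, grades 1 and 2 give the same answer. The overlap created by that route therefore alters the recorded intensity and not the dose. The Part 2 matrix behaves the same way: the dose is repeated after a grade 1 or resolved grade 2 event, and a related grade 3 event stops the patient. Only the choice between grade 3 and a lower grade changes the decision for a resolved event.

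Grades 1 and 2 do differ for unresolved events. That matters only for the last row of the first table (treated but not interfering), and only on the parse that lets such an event count as grade 1.

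**Step 3. What could one missed stop do to the MSD?** This is an illustration. Assume that two patients reach 720 mg (level 14), and that the third's maximum would have been *d* but the stop is missed and this patient also reaches 720 mg.

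MSD with the stop = (*d* + 2 × 720) / 3

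- *d* = 180 mg: 1620 / 3 = 540 mg
- *d* = 300 mg: 1740 / 3 = 580 mg
- *d* = 480 mg: 1920 / 3 = 640 mg

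Without the stop the MSD is 720 mg. The differences are 180, 140 and 80 mg. Assuming that the patient goes on to the top level makes these the largest differences for each *d*.

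**The case against.** The strongest reply is that the wording has little practical effect. Escalating through resolved moderate events is the stated design (section 6.1.1), so the grade 1/2 overlap costs nothing in dosing. Several checks do not depend on the grade. Any SAE stops the patient, with one narrow exception for unrelated events (section 8.3). Important medical events should usually be classed as serious (section 10.1). The Internal Monitoring Committee, which includes an external physician, reviews safety weekly and must agree unanimously for each patient (section 1.6). The treating physician may withdraw a patient on medical judgement (section 7.3).

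Most of this stands, and it limits the point. It does not remove it. A brief event without hospitalisation becomes an SAE only by judgement, and the committee has only this table to grade with. Nor does an unchanged dose decision correct the intensity table.

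A reader might infer more than the documents support:

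- *That the scale records infusion-related confusion as mild and so lets the dose rise.* Such an event can be recorded as mild, but it meets grade 2 as well. A resolved grade 2 event allows the increase anyway.
- *That an untreated event can never be grade 3.* The first sentence of grade 3 leaves that open.
- *That section 3.7 expects a transient, untreated course.* It says only that the infusion could be stopped. It does not describe recovery, and the projected half-life is 30 h (section 6.1.2).
- *That intensity is itself a primary outcome.* Section 5.1 lists the occurrence of AEs and SAEs and out-of-range laboratory values. Intensity enters through the tabulation in section 11.4.2.
- *That counting resolution in both the grade and the matrix distorts the decision.* Related grade 1 events allow the increase whether or not they have resolved, so there is no double effect.

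**Conclusion.** The grades are not mutually exclusive, and this should be corrected. The overlap between grades 1 and 2 for transient, untreated events without sequelae is certain from the text. Its effect is confined to the recorded intensity, which can be understated in the primary safety tables. How often that would happen cannot be estimated from the protocol.

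Any effect on dosing is conditional. It needs a related, severe, untreated event that is not classed as serious, that one reader would grade 3 and another lower, and that the committee lets pass. In that case one of the three values behind the MSD changes. Under the assumptions in the illustration, the Part 2 dose would be 80 to 180 mg higher than with the stop. The documents do not show that this would occur, and they do not support a claim that the grade 1 wording by itself drives escalation.

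**What to change.** **Grades 1 and 2.** Base both on functional impact while the event lasted. Delete the transient, untreated, no-sequelae clause as a separate route to grade 1. Keep duration and resolution as the items already recorded under section 9.2.1 and as the matrix column in section 8.3. As the working shows, this leaves the matrix decision for resolved events unchanged.

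**For the sponsor to reconcile.** Three points could move a delay or stop threshold, so no answer is proposed here:

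- how the medical significance criterion in grade 3 relates to the condition that treatment is required;
- whether stopping the infusion counts as treatment;
- which grade applies to an event that needed symptomatic treatment but did not interfere with usual activity.

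The answers must agree with sections 3.7, 6.1.1 and both matrices in section 8.3. No dosing or stopping rule is suggested.

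**Cost.** A wording amendment to one table and to the eCRF completion guidance. Some brief events will move from mild to moderate in the tables, so the profile may look slightly less favourable.
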